### Criteria for group sessions at the hospital

The hands of parents and their children will be washed before the activities start to avoid infectious contamination. Children will be divided into two groups as below:
1.Six months to 30 months old2.31 months to 60 months.

The intervention delivery details are as below:

On first day of hospitalization, parents and children will be interacted at Paediatrics ward. Randomization will be done and the parents in intervention arm will be sensitized about Play Therapy Programme. Written informed consents of parents will be taken from those who consent for participation and will be enrolled in the programme and e-learning platform/Whatsapp group.

On second day of hospitalization, a session will be conducted at designated play area in hospital. The session will emphasize on importance of early child development, its implications; diet, nutrition and healthcare of children. This session will be followed by play interaction session on cognitive and language development.

On third day of hospitalization, a play session on motor developmental activities will be conducted. This will be followed by session on socioemotional development and activities to promote it. Relevant Documents and reading materials in local language will be shared with parents during these sessions. The enrolled children will participate in play sessions and activities till the child is hospitalized.

After discharge from the hospital, parents and children will be contacted through monthly home visits personally and if needed, through online mode (Whatapp video call/Google classroom) at monthly intervals. The home visits will be scheduled for the assessment of Home Environment and Parent-Child Interactions. The monthly sessions will be continued till one year from the date of enrolment of child in the programme. Appropriate medical and nursing care will be provided during the hospital stay. If needed, referral services will be provided during follow-up at-home visits. If Children and parents insist on discontinuing play therapy, the sessions will be discontinued for those children.

After one-year of enrollment, assessments of age-appropriate developmental milestones of children will be done either in the hospital ECD Centre or through personalized home visit to the enrolled family. Age-appropriate assessment tools will be used. Reports will be shared with parents, and follow-up instructions and meeting schedules will be shared.

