**Figure 2. f2:**
[figure not shown]
The schedule of enrolment, interventions, and assessments.

The participants from control group will not receive any messages on any aspects of intervention, neither they will be interacted directly by intervention team throughout the study period. The control group participants will be contacted by the assessors for the baseline and endline assessments only.

There is no anticipated harm from the trial participation. The study participants will be provided with the printed copies of Play Therapy Manuals after completion of trial. The children with below average development scores will receive additional ECD services at hospital ECD centre and will receive follow-up till next one year through home visits.

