### Outcomes

*Primary outcomes:*
1.Improvements in mean scores of child developmental parameters for cognitive, physical, socio-emotional, and language development by the end of one year of intervention.2.Improvements in knowledge and skills of parents regarding early child development by the end of one year of intervention.

*Secondary outcomes:*
1.Improvements in the parent-child satisfaction levels regarding the in-hospitalization care and follow-up by the end of one year of intervention.

Figure 2 details the schedule of enrolment, interventions, and assessments.

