### Sample size

With reference to the study conducted by Gaidhane
*et al.,
*
^
25
^
^,^
^
26
^ the expected difference in child development outcomes between the intervention and control groups is 0.5 SD, considering a dropout rate of 10%, level of significance = 5%, and power = 80%. The formula for calculating sample size for two independent means is:

$$n=\frac{2\;{\left(\mathrm{Z\alpha}+\mathrm{Z\beta}\right)}^{2}\times \delta^{2}}{d^{2}}$$
where

n = Minimum sample size required in each group,

d = Expected mean difference between two groups = 0.5

δ = standard deviation = 1.69 (As per Previous Study)

Zα: value of type I error at 5% significance level =1.96

Zβ: value of type II error at 80 % Power (1-β) = 0.84

Based on the above formula, the calculations are as follows:

$$\begin{array}{c} n=\frac{2\;{\left(1.96+0.84\right)}^{2}\times 1.69^{2}}{{\left(0.5\right)}^{2}}\\ =\frac{2\left(7.84\right)\times 2.86}{0.25}\\ =\frac{44.84}{0.25}=179.37\approx 180 \end{array}$$

Thus, the sample size required per group is 180. Hence total sample size required is 360. A sample size of 360 subjects, 180 in each arm, is sufficient to detect a difference of 0.5 between groups in developmental scores, assuming a standard deviation of 1.69 using a two-tailed t-test of difference between means with 80% power and a 5% level of significance. For assessing the changes in parenting knowledge and skills, parents of all children in intervention group
**(180)** will be assessed.

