### Assignment of interventions: allocation

All participants consenting to participate in the study will be assigned the Unique ID. Sequence generation will be done using computer generated random numbers. Using a block randomization process
^
10
^
^,^
^
11
^ with age groups as the blocking variable, participants will be allocated either to intervention or control groups.

Sequentially numbered, opaque, sealed envelopes will be used for implementing the allocation sequence.

The Principal Investigator will generate the allocation sequence, trained assistants will enroll the participants, and assign participants to intervention and control groups. The Principal Investigator will train the Research Assistants for intervention, and assessors for baseline-endline assessments, supervise the data collection process and monitor the trial implementation process. We will ensure that all adults associated with the trial have the appropriate permissions and training and criminal records check to work with children. The outcome assessors and data analysts will be blinded.

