### Data collection and management

Data will be collected in pre-tested Open Data Kit (O.D.K.) based app with inbuilt checks for data quality, identifying duplicate entries. The data received on dedicated server of Research Cell of Datta Meghe Institute of Medical Sciences will be imported and checked on real time basis. The data will be encrypted for sensitive information and will be handled by the assigned team including Information Technology Coordinator and statistician. The datasets will be shared and made reusable according to FAIR data principles.

Assessments will be conducted using the tools as detailed below:
1.Physical Development (Using Developmental Milestones Checklist-II)
^
27
^
^,^
^
28
^
a.Improvement in Fine Motor scoresb.Improvement in Gross Motor scores2.Cognitive Development Scores (Using Developmental Milestones Checklist-II)3.Language Development Scores (Using Developmental Milestones Checklist-II)4.Socioemotional Development Scores (Using Profile of Socio-emotional Development)
^
29
^
5.Home Environment (Using HOME Inventory Assessment)
^
30
^
^–^
^
32
^
6.Parent-child Interactions (Using Observation of Mother-Child Interaction Tool)
^
33
^

The research assistants will be trained on the use of all these tools and inter-rater, intra-rater scoring exercises will be conducted during training. To promote participant retention and complete follow-up, all enrolled children in the intervention group will receive scheduled home visits at monthly intervals. The children in the control group will be followed up telephonically at monthly intervals. Also, telephonic follow-up will be taken for those missing home visits in intervention group. The outcome data will detail the participants who discontinue or deviate from intervention protocols.

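### Parental knowledge and skills, a primary outcome, is to be assessed in the intervention arm only; this conflicts with the unqualified blinding statement and puts blinding of the child scores at risk

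*Protocol article*

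**What the plan says.** Under Assignment of interventions: allocation, the protocol article says "The outcome assessors and data analysts will be blinded". The sentence covers all outcomes and all analysts, and no procedure is attached to it.

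The Outcomes section lists as its second primary outcome "Improvements in knowledge and skills of parents regarding early child development by the end of one year of intervention". The last sentence of the Sample size section sets who contributes to it: "For assessing the changes in parenting knowledge and skills, parents of all children in intervention group", with 180 given as the number to be assessed. Control parents are not mentioned there.

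On staffing, the allocation section distinguishes two roles: "The Principal Investigator will train the Research Assistants for intervention, and assessors for baseline-endline assessments". The text after Figure 2 keeps the control arm away from the intervention team: "The control group participants will be contacted by the assessors for the baseline and endline assessments only". Under Data management, each participant has one Unique ID, which is used for analysis and reporting.

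**The concern.** An assessment given in one arm only is itself a marker of arm. If it is planned for every intervention family and no control family, its presence or absence tells the holder of the record which group the child is in. The blinding statement makes no allowance for this.

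Two things are at stake. First, the parent outcome cannot be assessed blind, although the article says that outcome assessors are blinded. Second, the child development scores could lose their blinding through the same cue. They come from a milestones checklist and a socio-emotional profile, where a rater's expectation can affect scoring. On the analysis side, the Statistical methods section leaves open an iterative algorithm or multiple imputation for missing data, and adjusted and subgroup analyses. Masking the analyst is meant to protect choices of that kind.

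**Working it through.** **1. The plan's own figure.** Inputs from the Sample size section: difference 0.5, SD 1.69, z-values 1.96 and 0.84. n = 2 × (1.96 + 0.84)² × 1.69² / 0.5² = 2 × 7.84 × 2.8561 / 0.25 = 179.1, rounded up to 180 per arm. This agrees with the stated 180 per arm and 360 in total. It is context only, since the blinding point does not depend on it.

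**2. The statements side by side.**
- Allocation section: assessors and analysts are blinded, with no exception.
- Outcomes section: parental knowledge and skills is a primary outcome.
- Sample size section: that outcome is assessed in the parents of the intervention children.

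Taken together, the person assessing any parent for this outcome knows that the family is in the intervention arm. For this outcome the blinding statement fails however the staff are organised.

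**3. What the parent record reveals about the child.** By design, before dropout, a parent record exists for 180/180 = 100% of intervention families and 0/180 = 0% of control families. Seen beside the child scores, it classifies 180 + 180 = 360 of 360 children.

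**4. Whether it is seen beside the child scores.**
- Assessors: the article names one group for baseline and endline assessments and no separate assessor for parents. It does not say that each assessor gives every instrument.
- Analysts: one Unique ID serves the analysis, and the article describes neither a joint file nor a separate one for parent data.

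Neither link is stated, and neither is excluded.

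**5. Which assessments are one-arm.** Only parenting knowledge and skills. Data collection and management also lists the HOME inventory and a mother-child interaction tool, and that list does not restrict them to one arm.

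**6. Illustration of what unblinded scoring could do.** The shifts are assumed; the documents give none. Suppose that knowing the arm moves the mean difference by b SD in favour of the intervention when there is no true effect. With 180 analysed per arm, SE = 1.69 × √(2/180) = 0.178. The expected z is k = b × 1.69 / SE, and the two-sided 5% test rejects with probability 1 − Φ(1.96 − k) + Φ(−1.96 − k).

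| Assumed b (SD) | Points | Share of 0.5 | k | Rejects a true null |
|---|---|---|---|---|
| 0.05 | 0.08 | 17% | 0.47 | 7.6% |
| 0.10 | 0.17 | 34% | 0.95 | 15.8% |
| 0.20 | 0.34 | 68% | 1.90 | 47.5% |

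With the 10% dropout that the Sample size section mentions, 180 × 0.9 = 162 per arm and SE = 1.69 × √(2/162) = 0.188. The values of k become 0.45, 0.90 and 1.80, and the rates 7.3%, 14.7% and 43.7%.

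**The case against.** The strongest reply is that nothing in the article places parent and child data in the same hands. Assessors are separated from the intervention team. Intervention staff could assess the parents, and the child scores could be analysed from a file that holds no parent data. The sentence in the Sample size section fixes how many parents are assessed, not by whom or when. How analysts are masked is commonly left to the full protocol or analysis plan, neither of which is shown.

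Much of this stands. A reader might infer that blinding of the child scores cannot hold whoever the assessors are. The documents do not support that, because a separate parent assessor and a separate file would preserve it. The absence of dummy codes or split exports from a journal article is not a fault in itself.

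A reader might also see a second marker of arm in the sentence "The outcome data will detail the participants who discontinue or deviate from intervention protocols". That does not carry the point. Recording discontinuations and deviations is ordinary trial practice, puts nothing on an assessor's form, need not enter the file used for the blinded analysis, and would flag only some children, a number the article does not give.

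The rejection rates are also open to challenge. They rest on assumed shifts in one direction, concern scoring only, and say nothing about an unblinded analyst.

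The reply does not remove the conflict between two rules the article does state: blinding for all outcome assessors, and a primary outcome assessed in one arm. Nor are the roles cleanly separated in the text. The intervention is delivered by research assistants, yet Data collection and management says "The research assistants will be trained on the use of all these tools", and the section on hospital sessions adds, in describing intervention delivery, "The home visits will be scheduled for the assessment of Home Environment and Parent-Child Interactions".

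**Conclusion.** The point holds in limited form. For parental knowledge and skills, the blinding statement is contradicted by the rule that only intervention parents are assessed. This needs no assumption beyond reading the Sample size sentence as it stands. For the child outcomes, blinding is at risk: the arm of all 360 children is revealed if the same assessors, or one linked file, carry both parent and child data, and of none by this route if the two are kept apart. The article does not settle which applies.

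The false-positive rates of 7.6% to 47.5% only illustrate how sensitive the test is to assumed scoring shifts of 0.05 to 0.2 SD. They are not estimates of bias in this trial.

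The same rule has a second consequence: with no control parents assessed, this primary outcome has no between-arm comparison. The plan should be changed on both grounds.

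**What to change.** Amend the Sample size sentence so that parental knowledge and skills are assessed in both arms at the scheduled baseline and endline assessments. At each contact, complete the child tests and lock their scores in the app before the parent questionnaire is opened. This removes the arm cue and gives the parent outcome a control group. The cost is a short questionnaire for up to 180 control parents at contacts the article already plans, plus a rule on form order.

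If the assessment stays in one arm, have it given by staff who do not score the children, keep it out of the file used for the blinded child-outcome analysis, and limit the blinding statement to the child outcomes. This costs little, but the parent outcome would still lack a between-arm comparison.

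The Trial status section expected completion on 30 May 2024. If control parents can no longer be assessed, what remains is the separate file, if the analysis has not yet been run, and a blinding statement that describes what was actually done.

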### Data collection and management

Data will be collected in pre-tested Open Data Kit (O.D.K.) based app with inbuilt checks for data quality, identifying duplicate entries. The data received on dedicated server of Research Cell of Datta Meghe Institute of Medical Sciences will be imported and checked on real time basis. The data will be encrypted for sensitive information and will be handled by the assigned team including Information Technology Coordinator and statistician. The datasets will be shared and made reusable according to FAIR data principles.

Assessments will be conducted using the tools as detailed below:
1.Physical Development (Using Developmental Milestones Checklist-II)
^
27
^
^,^
^
28
^
a.Improvement in Fine Motor scoresb.Improvement in Gross Motor scores2.Cognitive Development Scores (Using Developmental Milestones Checklist-II)3.Language Development Scores (Using Developmental Milestones Checklist-II)4.Socioemotional Development Scores (Using Profile of Socio-emotional Development)
^
29
^
5.Home Environment (Using HOME Inventory Assessment)
^
30
^
^–^
^
32
^
6.Parent-child Interactions (Using Observation of Mother-Child Interaction Tool)
^
33
^

The research assistants will be trained on the use of all these tools and inter-rater, intra-rater scoring exercises will be conducted during training. To promote participant retention and complete follow-up, all enrolled children in the intervention group will receive scheduled home visits at monthly intervals. The children in the control group will be followed up telephonically at monthly intervals. Also, telephonic follow-up will be taken for those missing home visits in intervention group. The outcome data will detail the participants who discontinue or deviate from intervention protocols.

### Data management

All data will be collected in tablet P.C. based O.D.K. collect app with an in-built range check, double entry, and value checks. Data will be exported to the server after ensuring the correctness of the data entered. The data from the server can be downloaded as an excel file. Each participant will be allotted a Unique ID which will be used for analysis and reporting purposes. All data will be anonymous and personal information will be maintained to protect confidentiality before, during, and after the trial.

### Statistical methods

After appropriate cleaning and compilation, the pre- and post-intervention child development data in specified domains will be collected and fed to STATA-14 by the assigned statistician. Individual and child age-group wise scores of developments will be calculated and tabulated. Mean differences in child development scores for intervention and control groups and pre-post intervention will be calculated. The effect size by Cohen’s-D will be calculated for each child age group, and significance of differences in effect size will be estimated. Also, qualitative subgroup and adjusted analyses, Difference in difference analysis for motor, language, cognitive and socio-emotional development scores will be done. Attempts will be undertaken to ensure the collection of complete data. In cases of missing data, families will be contacted through home visits and missing data will be collected. If any case/family could not be tracked, iterative algorithm or multiple imputation technique will be used to handle the missing data. The datasets analysed during the current study, statistical code and full protocol will be made available by publishing on open data repository Zenodo.

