### Recruitment

Parents of children reporting to A.V.B.R.H. in the first three months (January-March 2023) will be enrolled in the trial. All participants consenting to participate in the study will be assigned the Unique ID. Using a blocked randomization process with age groups as the Blocking variable, participants will be allocated to intervention or control groups. Age groups will be:
1.Six months to 30 months2.31 months to 60 months.

All children hospitalized in A.V.B.R.H., scheduled to stay for a minimum of three days in the hospital, and their parents signed the informed consent will be enrolled in the study.

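### The trial is sized on one whole-arm comparison, but its only significance statement concerns effect sizes by age group; a whole-sample ANCOVA per domain should be named as primary

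*Protocol article*

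**What the plan says.** The Sample size section of the protocol article derives 180 children per arm for a comparison of two whole arms, "using a two-tailed t-test of difference between means with 80% power and a 5% level of significance". The formula uses "d = Expected mean difference between two groups = 0.5" and a standard deviation of 1.69. The opening sentence of the same section says that "the expected difference in child development outcomes between the intervention and control groups is 0.5 SD".

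The Outcomes section makes four child domains primary: "Improvements in mean scores of child developmental parameters for cognitive, physical, socio-emotional, and language development". Children aged 6 to 60 months are randomised in two age strata, 6 to 30 and 31 to 60 months (Recruitment section: "Using a blocked randomization process with age groups as the Blocking variable").

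The Statistical methods section then lists what will be done. "Mean differences in child development scores for intervention and control groups and pre-post intervention will be calculated". Cohen's d "will be calculated for each child age group, and significance of differences in effect size will be estimated". Subgroup analyses, adjusted analyses with no covariates named, and difference-in-differences for the motor, language, cognitive and socio-emotional scores follow. Nothing in the list is called primary, and the t-test behind the sample size does not appear in it.

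**The concern.** Three things do not fit together.

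- **The tested quantity is not the one the trial was sized for.** The only sentence in Statistical methods that mentions significance is about age-group effect sizes. It can mean a between-arm test inside each age group, or a test of whether the effect differs between the groups. Neither is the 180 v 180 comparison, and the second is not an estimate of the treatment effect at all.
- **The one named whole-sample method that uses the baseline is difference-in-differences.** In a randomised trial, ANCOVA uses the same data at least as efficiently.
- **Pre-post change stands beside the between-arm difference, unranked.** Over a year, children who enter at 6 to 60 months gain skills in both arms, so change within an arm mostly reflects growth and is not a treatment effect.

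At stake is which result answers the primary question. If the age-group results were read as the main test, a real effect of the size planned for could be missed about half the time. With four primary domains and no ranking, it is also open which positive result would count.

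**Working it through.** **Inputs from the Sample size section:** difference 0.5, SD 1.69, two-sided 5%, 80% power, 180 per arm. **Assumptions, because the protocol gives no figure:** the age strata are equal (90 per arm in each), the SD of 1.69 applies within each stratum, the SD is the same at baseline and 12 months, and the correlation r between baseline and 12-month score is 0.3, 0.5 or 0.7. Powers use the normal approximation, Φ(difference/SE − 1.96).

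**1. The plan's own figure.** n = 2 × (1.96 + 0.84)² × 1.69² / 0.5² = 15.68 × 2.8561 / 0.25 = 179.1, so 180 per arm. The stated size is reproduced. Power at 180 per arm: SE = 1.69 × √(2/180) = 0.178; 0.5/0.178 = 2.807; Φ(0.847) = 80.1%.

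**2. Between-arm test within one age group.** SE = 1.69 × √(2/90) = 0.252; 0.5/0.252 = 1.985; Φ(0.025) = 51.0%. With an unequal split, power is 36.7% at 60 per arm and 63.0% at 120 per arm.

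**3. Difference in effect between the two age groups.** SE = 1.69 × √(4/90) = 0.356. For a 0.5-point difference, 0.5/0.356 = 1.403; Φ(−0.557) = 28.9%.

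**4. The other reading of the effect size.** With 0.5 SD, one age group at 90 per arm has 0.5/√(2/90) = 3.354; Φ(1.394) = 91.8%. The whole sample has 99.7%. The loss in step 2 therefore depends on 0.296 SD, which is the only reading that yields 180 per arm.

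**5. Difference-in-differences against ANCOVA, 180 per arm.** The variance, relative to a comparison of 12-month scores alone, is 2(1 − r) for difference-in-differences and 1 − r² for ANCOVA. The gap is 2(1 − r) − (1 − r²) = (1 − r)², which is never negative.

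| Assumed r | 12-month scores only | Difference-in-differences | ANCOVA | ANCOVA at 0.05/4 |
|---|---|---|---|---|
| 0.3 | 80.1% | 66.0% | 83.7% | 67.2% |
| 0.5 | 80.1% | 80.1% | 90.0% | 77.1% |
| 0.7 | 80.1% | 95.2% | 97.6% | 92.4% |

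The last column is the first step of a Holm procedure over four domains.

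**6. Four domains at 5% each.** If the tests are independent, the chance of at least one false positive is 1 − 0.95⁴ = 18.5%. By simulation it is 15.6% if the tests correlate at 0.5.

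**The case against.** The strongest reply is that the list in Statistical methods is not a hierarchy. It includes between-arm mean differences and adjusted analyses, and an analysis plan that is not shown may rank them and name covariates. That stands. A reader might infer that the trial's inference rests on the age-group tests and that its headline result has half the stated power. The protocol does not say so. It attaches the word significance to those effect sizes and leaves the rest unranked.

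A reader might also infer that an unadjusted comparison loses the planned power. It does not: it is the very test that gives 80% at 180 per arm. Nor does difference-in-differences always lose. It falls below a comparison of 12-month scores only when r is under 0.5, and no correlation is given. At r = 0.7 it is within about 2.4 percentage points of ANCOVA (97.6 − 95.2).

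On multiplicity, the Trial design section calls the trial exploratory. Outcomes lists four child domains, with physical development as one of them, and the Discussion's description of success sets no rule that any single domain suffices. Counting fine and gross motor separately in each age group, to reach ten primary tests, goes beyond the text.

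The reply does not remove the mismatch between the sized comparison and the one significance statement. An analysis plan that made the whole-arm comparison primary would have to demote the age-group wording.

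**Conclusion.** The point holds as a mismatch that should be corrected and an efficiency gain available at no cost. It does not show that the trial is underpowered. On the sample-size formula's own inputs, the comparison tied to the word significance has about 51% power (within an age group) or 29% (between age groups), against 80% for the comparison that was sized. ANCOVA is at least as powerful as difference-in-differences at every correlation. The gain is about 18 points at r = 0.3, 10 at r = 0.5 and 2 at r = 0.7.

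The age-group figures rest on equal strata, on 0.296 SD, and on the SD of 1.69 applying within a stratum; a smaller within-stratum SD would raise them. Under 0.5 SD the figure within an age group is about 92%, so the protocol's two statements of the effect size have to be reconciled before the loss can be called firm. The efficiency comparison takes allocation to be randomised, as the Trial design section says.

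Multiplicity is a secondary point: up to 18.5% over four domains, softened by the exploratory label. ANCOVA does not cure it.

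**What to change.** - **Primary analysis.** For each domain, in all randomised children: ANCOVA of the 12-month score on arm, baseline score and age, with the age-group stratum in the model. Report the adjusted mean difference with its 95% confidence interval, and Cohen's d alongside.
- **Age groups.** Secondary, through one arm-by-age-group interaction per domain, with the effect in each group shown for description.
- **Pre-post changes.** Descriptive only. Difference-in-differences, if kept, is a supporting analysis.
- **Several domains.** State that success will not be claimed on any single domain unadjusted. Holm is one option, but it is a trade-off: its first step over four domains leaves ANCOVA power at about 67%, 77% and 92% for r = 0.3, 0.5 and 0.7, so 80% is recovered only at a fairly high correlation.
- **Effect size.** Say whether the planned difference is 0.5 points or 0.5 SD.

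The cost is wording. Age and baseline scores are already collected in both arms. Recruitment began in January 2023 and completion was expected in May 2024, so the change should be dated and made before anyone analyses outcomes by arm; if that has already happened, it should be reported as a later decision.
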